### Inclusion and exclusion criteria

Patients suitable for inclusion were those who satisfied the criteria for excessive health anxiety above and were (i) aged between 16 and 75, (ii) permanently resident in the area, (iii) had sufficient understanding of English to read and complete the questionnaires, and (iv) had given written consent for the interviews, audio-taping of 50% of treatment sessions, and for access to their medical records. The presence of existing medical pathology, provided it was not new and requiring further investigation, was not a bar to treatment in the study. This decision was made as in an earlier study we found that many patients with existing pathology who also had high health anxiety benefited from the intervention [10].

Some of those who would otherwise satisfy the inclusion criteria above were excluded if (i) they were felt by their consultants to have a level of continuing major pathology that was too severe for them to take part in the study, (ii) they were currently being actively investigated for significant pathology suspected by the clinician and for whom cognitive behaviour therapy might confuse or cause distress, (iii) they had significant cognitive impairment, and (iv) they were currently under psychiatric care.

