The remaining clinical assessments, in addition to the main health anxiety one (HAI) examined the presence of generalised anxiety and depression (measured with the HADS scale [14]) as these are common in patients with hypochondriasis, and also adversely affects quality of life (EQ-5D)[15], and social functioning (SFQ)[16]. These assessments were given at baseline and at 6m, 12m and 24m (or earlier and at intervening periods if drop-out or loss to follow-up was likely). To ensure the highest possible follow-up the intention was to contact patients after 18 months to be reminded of the 2 year assessment, and if for any reason (eg being out of the country), the final assessment might be made earlier. The HAI was also given at 3 months by post or by telephone with a research assistant. Service use data for the economic evaluation was collected using the Adult Service Use Schedule (AD-SUS), an interviewer-assessed instrument designed by one of the applicants and based on previous economic evaluations in adult mental health populations [22,23], and also by examination of computerised hospital records. AD-SUS data were recorded at baseline and at 6, 12 and 24 months. Where the AD-SUS data conflict with the data obtained from the computerised records the AD-SUS data will take precedence only when it refers to a contact at a hospital not included in the electronic data search, as the details of admission and investigations is more likely to be correct from official records than from personal retrospective recall. Data on workplace absenteeism and presenteeism [24] were also recorded at 6, 12 and 24 months follow-up. In addition the SCID-I hypochondriasis questions [17] are to be administered again at 24 months to determine if each patient still satisfies the requirements for DSM-IV hypochondriasis. All these instruments are given at face to face interview but also have the advantage that they can be given over the telephone if necessary, and this can be useful in reducing loss to follow up. All assessments are carried out by independent research assistants who have had no contact with the patient at other times and who are carefully masked to avoid disclosure of allocation (see below).

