## Statistical analysis

All primary statistical analysis will use the intention-to-treat principle. The primary endpoint will be analysed using a mixed model with time, treatment, time × treatment interaction as fixed effects, baseline measurement as covariate, and patient as random effect. The treatment difference at 12 months together with its 95% confidence interval will be derived from the mixed model.

Missing data will be treated as missing at random in the above mixed model analysis and no imputation will be made. To assess the sensitivity of the result to this assumption, the last observation carried forward (LOCF) strategy will be used to compute the missing HAI at during the follow up visits. Other assessments will be analysed in a similar way.

The primary economic evaluation will only include those for whom complete data at baseline, 12 and 24 months follow-up are available. Sensitivity analysis will then include those cases with missing data, where LOCF will be used to account for missing data. The following baseline characteristics of study participants with available and unavailable service use data will be compared: centre, gender, living arrangements, ethnicity, marital status, education, EQ-5D.

For each piece of service use information collected with the AD-SUS, a unit cost will be applied and the total costs calculated. The total cost per participant is calculated by summing all costs. All unit costs will be for the financial year 2008-2009. Costs in the second year will be discounted at a rate of 3.5%, as recommended by the National Institute for Health and Clinical Excellence [28].

The difference in mean costs between active treatment and control groups together with the 95% confidence interval will be derived. The equivalence margin is pre-specified as £150. The equivalence will be declared between active and control groups in terms of secondary economic outcome if the 95% confidence interval falls within (-£150, +£150).

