Even in situations where equivalence or non-inferiority are demonstrated, exploration of the joint distribution of costs and effects in a cost-effectiveness analysis (CEA) is recommended to represent uncertainty [29] and to help interpret the economic results. For these reasons, we propose to undertake a CEA irrespective of whether or not non-inferiority in the primary clinical outcome is demonstrated. Cost-effectiveness will be assessed using the net benefit approach [30] with reference to Bosmans' methods (31) for economic evaluations alongside equivalence or non-inferiority trials.

The cost-effectiveness analysis will use the primary outcome measure the HAI and a cost-utility analysis will be completed using QALYs derived from the EQ-5D data. A number of one-way sensitivity analyses will test the robustness of the results to the assumptions made in the economic evaluation.

The numbers (with percentages) of losses to follow-up at 12, and 24 months after randomisation will be reported and compared between the treatment arms with absolute risk differences (95% Confidence Intervals). Deaths will be reported separately for each group. The CONSORT procedure will be used for reporting flow through the trial.

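### The complete-data and LOCF rules for the economic evaluation make no exception for deaths; applied as written, they drop patients who die before 24 months and then carry their costs and utility past death

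*Protocol article*

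**What the plan says.** The Statistical analysis section of the protocol article fixes two rules for the economic evaluation. The analysis set is: "The primary economic evaluation will only include those for whom complete data at baseline, 12 and 24 months follow-up are available". The back-up is: "Sensitivity analysis will then include those cases with missing data, where LOCF will be used to account for missing data". The utility analysis rests on the same visits: "a cost-utility analysis will be completed using QALYs derived from the EQ-5D data".

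The only sentence on death, later in that section, concerns reporting: "Deaths will be reported separately for each group". It comes after a separate sentence on attrition: "The numbers (with percentages) of losses to follow-up at 12, and 24 months after randomisation will be reported and compared between the treatment arms".

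The Assessments section names two sources of resource use. The first is an interview: "Service use data for the economic evaluation was collected using the Adult Service Use Schedule (AD-SUS), an interviewer-assessed instrument". The second needs no respondent: "and also by examination of computerised hospital records". Where the two conflict, the hospital records prevail, except for contacts at hospitals outside the electronic search. AD-SUS and EQ-5D are both scheduled at baseline and at 6, 12 and 24 months.

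**The concern.** Death differs from loss to follow-up because the outcome after it is known: no further service use and a utility of zero. A rule written for unobserved data gives a wrong answer when applied to these patients.

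Deaths cannot be ruled out in this population. Patients are aged up to 75, come from cardiology, respiratory and other medical clinics, and are followed for two years. On comorbidity the article says: "The presence of existing medical pathology, provided it was not new and requiring further investigation, was not a bar to treatment in the study".

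What is at stake is the economic conclusion. Equivalence is declared only if the 95% confidence interval for the difference in mean cost lies within £150 either side of zero, and the trial was sized on that comparison. The margin is narrow beside the cost of a hospital admission, so a few patients with expensive final months can matter. Replacing LOCF with another imputation method would not help, because it too would create values after death unless told not to.

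**Working it through.** **Applying the two rules to a patient who dies at month 18**

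- *Primary analysis.* There is no 24-month AD-SUS interview and no 24-month EQ-5D. On an ordinary reading the data are not complete, so the patient is left out, and hospital costs incurred up to month 18 go too, even though the computerised records can supply them.
- *Sensitivity analysis.* The patient returns as a case with missing data. The last recorded cost and EQ-5D are carried to month 24, so six months after death receive cost and, if the last utility was positive, quality-adjusted time.
- *Elsewhere in the article.* No sentence sets cost or utility to zero after death, and the sentence on deaths governs reporting only.

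The article states no figure on this point, so there is none to reproduce. The sizes below are illustrations.

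**Inputs from the article:** 444 randomised, taken as 222 per arm; equivalence margin £150; cost SD £580; 186 completers per group planned.

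**Assumed inputs:** cost before death £5,000 to £10,000; mean cost of other patients between £0 and £580; utility before death 0.4 to 0.8; difference between arms in the share who die 0.5 to 2 percentage points.

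**1. Leaving one death out of an arm of 222.** The shift in the arm mean is (C − m)/n, where C is the cost of the patient who dies and m the mean of the others.

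| | C = £5,000 | C = £10,000 |
|---|---|---|
| m = £580 | 4,420/222 = £19.9 (13% of £150) | 9,420/222 = £42.4 (28%) |
| m = £0 (upper bound) | 5,000/222 = £22.5 (15%) | 10,000/222 = £45.0 (30%) |

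With the planned 186 per group as denominator, the upper-bound row becomes 5,000/186 = £26.9 (18%) and 10,000/186 = £53.8 (36%). These are shifts in one arm. They become shifts in the difference only when the other arm has no matching death; with equal deaths and equal costs the net effect is about £0.

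**2. Carrying cost past death.** The bias in the between-arm difference is the difference in death share times the amount carried per death.

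- Low: 0.005 × £580 = £2.9 (2% of the margin).
- High: 0.02 × £5,000 = £100 (67%).

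**3. Carrying utility past death for one year** (death at month 12).

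- One death in an arm of 222 with utility 0.6: 0.6/222 = 0.0027 QALY on the arm mean.
- Between arms: 0.005 × 0.4 = 0.002 to 0.02 × 0.8 = 0.016 QALY, undiscounted.

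**4. What correct inclusion does to the interval** (222 per arm, m = £580, other patients equal on average in the two arms).

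- No death: half-width 1.96 × 580 × √(2/222) = £108.
- One £10,000 case in one arm: that arm's SD is √(580² + 9,420²/222) = √(336,400 + 399,713) ≈ £858. The half-width is 1.96 × √((336,400 + 736,113)/222) ≈ £136, and the difference is £42. The upper limit is about 42 + 136 = £179 after rounding, outside the margin.
- One £5,000 case in one arm: SD √(336,400 + 4,420²/222) ≈ £651, half-width 1.96 × √((336,400 + 424,402)/222) ≈ £115, difference £20. The upper limit is about £135, inside the margin.

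Under these assumptions, whether one patient is counted can decide the equivalence result.

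**The case against.** The strongest reply is that the article says nothing about how deaths enter the economic analysis, and that such a convention is usually left to a full protocol or analysis plan, which is not shown here. It also requires complete data, not a completed interview: a patient with hospital records to the date of death and known zeros afterwards could be called complete. This stands in part. That reading is possible, but the article does not state it, and it describes costing from AD-SUS items. Nor did the article leave missing economic data to another document: it specified both the analysis set and the fill-in method, and for a foreseen group those rules go wrong on their ordinary meaning.

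Other parts of the reply stand in full. Patients judged by their consultants to have pathology too severe for the study were excluded, as were those under active investigation for significant suspected disease, so deaths should be few. Every size above rests on assumed costs, utilities and death shares.

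Four stronger inferences are tempting and should be resisted:

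- *That the plan classes deaths as missing data.* It does not. The problem follows from general rules that lack an exception.
- *That deaths are counted as losses to follow-up.* The two have separate sentences, and the article can already be read as keeping them apart.
- *That dates of death are already collected.* The article says only that deaths will be reported.
- *That the sensitivity analysis would hide a difference between arms.* LOCF restores patients with the costs recorded at earlier visits, and carrying a high cost forward could exaggerate a difference just as well.

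**Conclusion.** The point holds as a defect in how two stated rules apply to a foreseen group. It is not a stated policy on deaths. As written, the rules exclude patients who die before 24 months from the primary cost and QALY analysis and carry values past death in the sensitivity analysis.

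The size cannot be known from the article. Under assumed pre-death costs of £5,000 to £10,000 and 222 per arm, each unmatched death moves an arm mean by roughly £20 to £45, or 13% to 30% of the margin; balanced deaths with similar costs leave the difference almost unchanged. The QALY effect is small, about 0.003 per death on an arm mean at an assumed utility of 0.6. The primary clinical analysis, a mixed model of HAI without imputation, does not use these two rules.

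**What to change.** Add a short rule to the economic analysis, or confirm that the full analysis plan already contains it:

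1. From death onward, cost is £0 and EQ-5D utility is 0.
2. Hospital costs up to death come from the computerised records.
3. Patients who die count as complete in the cost and QALY analyses.
4. No cost or utility is carried forward or imputed after death.

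The drafting cost is a few lines, best agreed before results by arm are seen so that the choice is not made after the fact. Three practical costs remain. Dates of death must be obtained, since the article does not say that they are recorded. The records cover only the hospitals in the electronic search, so the rule should say how other care, and utility, between the last assessment and death are handled. And including high pre-death costs widens the cost interval: in the illustration above, one £10,000 case raises an arm's SD from £580 to about £860 and makes equivalence harder to show. Those costs were incurred, so the wider interval is the more accurate one.

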## Background

Abnormal health anxiety - and its older synonym, hypochondriasis - is a relatively common problem in both primary and secondary medical care settings [1-3]. It also places a substantial burden on health services [4], as its central feature is sufficient fear of having a serious disease to lead to medical consultation, and, very commonly, this is followed by further investigations. This condition, despite its ubiquity and its ability to provoke considerable suffering, is often unrecognised or appreciated at a superficial level. Even when the condition is recognised, concerns over litigation may lead to expensive investigations being carried out unnecessarily. This may provoke further pathology when findings of marginal clinical significance are reported. The extra burden on services is particularly important in secondary medical care. Between 10 and 20% of all attenders at medical clinics have abnormal health anxiety [5-7] and patients often rotate between different clinics depending on the focus of their symptoms. The symptoms of abnormal health anxiety show little tendency to spontaneous resolution and persist for months in the absence of treatment [5].

The failure to detect this serious pathology is perhaps less surprising when there is a general belief that there is no adequate treatment. Pharmacological management is generally unsatisfactory but psychological treatment in the form of cognitive behaviour therapy (CBT) has been shown to be effective, mainly in primary care [8,9] and, more recently, in a secondary care medical clinic [10]. Although these trials suggest efficacy of this intervention, it is less clear if it has a significant impact on costs. Although the total costs were somewhat reduced in those receiving cognitive behaviour therapy in the only trial in secondary care, these only became manifest in the six months after treatment had been completed [10]. The CHAMP trial is the natural successor to these studies, and examines both efficacy and cost-effectiveness of this newly modified treatment over a two-year period.

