### Target population and procedure

Patients attending clinics of the collaborating consultants, apart from those who have been specifically excluded (see below), were approached while waiting for their out-patient appointments and given the short form of the Health Anxiety Inventory (HAI)[13], a rating scale of 14 questions that takes 5-10 minutes to complete. Those that scored at least 20 on the scale were offered the opportunity to take part in the trial and given an information sheet about the study. Within a week of receiving the information sheet and agreeing to be contacted the researcher administered part of the Structured Clinical Interview for DSM-IV with questions covering the diagnosis of hypochondriasis, and if the patient satisfied the criteria for this diagnosis he or she was invited to give formal consent and complete baseline assessments. At this appointment all patients received a standard explanation of the nature and significance of health anxiety that put their problem into context, and this was followed by the assessments described below. After completion of the assessments the research assistant entered and registered each patient to an on-line system (OpenCDMS Clinical Data Management System) and this was automatically followed by the appropriate randomisation. The study coordinator was then informed of the details of the treatment arm allocation and passed on the details to the next available therapist. Equal allocation was made to either (i) active treatment group - between 5 and 10 60-minute sessions of cognitive behaviour therapy from a graduate researcher, or trained research nurse or equivalent professional, at the clinic backed up by three booklets specially written for patients, or (ii) a control group of normal care who would not receive specific treatment but had already received a short account of the essentials of health anxiety at baseline interview.

The patients were recruited over a 21 month period beginning in October 2008 and each will be followed up for two years. In addition to research assistants who were employed on the trial, help in recruitment was also provided by Clinical Studies Officers of the North London and East Midlands hubs of the Mental Health Research Network.

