## Discussion

The CHAMP trial is the first large scale trial of cognitive behaviour therapy for health anxiety in secondary care. Although there is increasing evidence of the clinical benefits of this treatment in primary care [8,32,33] the added value of this treatment in secondary care in terms of cost-effectiveness is still uncertain, and explains the importance of the two year follow-up. This extends far beyond the time of treatment and will allow for the assessment of longer term cost savings as well as the maintenance of clinical benefit. Preliminary evidence from a study carried out in parallel with CHAMP, suggests that hospital cost savings are substantial when treatment is successful [34].

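### LOCF is an unsuitable way to fill missing costs in the economic sensitivity analysis: it misstates the 24-month total and distorts the between-arm difference by an amount and sign that cannot be known in advance

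*Protocol article*

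**What the plan says.** All of this is in the protocol article.

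- **Analysis set (Statistical analysis).** "The primary economic evaluation will only include those for whom complete data at baseline, 12 and 24 months follow-up are available". Incomplete cases enter only afterwards: "Sensitivity analysis will then include those cases with missing data, where LOCF will be used to account for missing data".
- **Endpoint (Statistical analysis).** "The total cost per participant is calculated by summing all costs". Second-year costs are discounted at 3.5%. "The equivalence margin is pre-specified as £150", and equivalence is declared if the 95% CI for the mean cost difference lies inside ±£150.
- **Data (Assessments).** "AD-SUS data were recorded at baseline and at 6, 12 and 24 months". Computerised hospital records are a second source of service use, and they take precedence except for hospitals outside the electronic search.
- **Timing of cost.** The active arm is offered "between 5 and 10 60-minute sessions of cognitive behaviour therapy" (Target population and procedure). Of the two-year follow-up the Discussion says: "This extends far beyond the time of treatment". Of the cost reductions in the pilot trial the Background says: "these only became manifest in the six months after treatment had been completed".

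The article gives no rescaling of carried costs for period length, does not keep CBT cost out of what is carried forward, and does not confine LOCF to the part that hospital records cannot supply.

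**The concern.** LOCF is meant for a level measured repeatedly, such as a symptom score. A cost is an amount accrued over an interval, and the endpoint is the sum of those amounts. Two problems follow.

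First, the intervals implied by the interview schedule are 6, 6 and 12 months, so a carried 6-month amount fills only half of the last slot.

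Second, the trial's own rationale gives the two arms different cost profiles: an early therapy cost and later savings in one arm only. Carrying an early value forward repeats the therapy cost or misplaces the savings in the CBT arm and does neither in the control arm. Equal drop-out does not cancel this.

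This is the only economic analysis described that includes incomplete cases, and 20% loss was planned for. If it disagrees with the complete-case result, nobody can tell an effect of missingness from an effect of the filling rule. If it agrees, the agreement reassures little.

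**Working it through.** **Inputs from the article.** Margin £150, SD £580, expected difference £0, 186 per group, 20% drop-out by 24 months, 466 in total; interviews at 6, 12 and 24 months.

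**Assumptions, not in the article.** Each form covers the time since the last. Control cost is a constant c per month. CBT cost K falls in months 0–6 and is fully offset later, so the true 24-month difference is £0. Drop-out is equal in both arms. Discounting is ignored. K = £250, £400 and £600 are illustrations only.

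**The plan's own figure.** 2 × 580² × (1.645 + 0.842)² / 150² = 185 per group, within one of the stated 186. Then 186 / 0.80 = 232.5, rounded up to 233 per group, or 466. (This is the formula for a single one-sided 5% test; how that sits with the 95% CI rule is a separate matter.)

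**Precision.** Half-width = 1.96 × 580 × √(2/n): £118 at n = 186 and £105 at n = 233. The room left inside ±£150 is £32 and £45.

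**Level.** A flat-cost patient truly costs 24c. Last seen at 6 or at 12 months, unscaled LOCF gives 6c + 6c + 6c = 18c, which is 25% too low.

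**Difference between arms.** Control periods are 6c, 6c, 12c.

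- *Savings spread over months 6–24.* CBT periods: 6c + K, 6c − K/3, 12c − 2K/3. Last seen at 6 months: 3(6c + K) = 18c + 3K, an excess over control of 3K. Last seen at 12 months: (6c + K) + 2(6c − K/3) = 18c + K/3, an excess of K/3.
- *Savings in months 6–12 only.* CBT periods: 6c + K, 6c − K, 12c. Last seen at 6 months: excess 3K. Last seen at 12 months: (6c + K) + 2(6c − K) = 18c − K, an excess of −K.

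Weighting by the share lost at each point gives the artefact (amounts for K = £250, £400, £600):

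| Lost after 6 / after 12 months | Savings over months 6–24 | Savings in months 6–12 |
|---|---|---|
| 10% / 10% | +K/3: £83, £133, £200 | +0.2K: £50, £80, £120 |
| 5% / 15% | +0.2K: £50, £80, £120 | 0 |
| 0% / 20% | +K/15: £17, £27, £40 | −0.2K: −£50, −£80, −£120 |
| 5% / 5% | +K/6: £42, £67, £100 | +0.1K: £25, £40, £60 |

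**Other ways of applying the rule.**

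- *Rescaling for period length.* With savings over months 6–24, loss at 6 months gives 4(6c + K), an excess of 4K, and loss at 12 months gives none. At 10% / 10% the artefact is 0.4K, larger than without rescaling.
- *Carrying the cumulative total.* With the same savings pattern, 0.1 × K + 0.1 × 2K/3 = K/6: £42, £67, £100. Later cost is set to zero.
- *Two yearly totals.* The 25% shortfall goes. With savings over months 6–24, year 1 carries an excess of 2K/3, which is doubled to 4K/3; with 20% lost after year 1 the artefact is 0.27K, or £107 at K = £400. With savings wholly in months 6–12 it is zero.

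**Effect on the decision.** At 233 per group, SD £580 and a true difference of £0, the chance that the 95% CI falls inside ±£150 is 59% with no artefact, 42% with £50 and 15% with £100.

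**The case against.** The strongest reply is that this is a sensitivity analysis. The primary economic evaluation is complete-case, no stated rule makes the equivalence verdict depend on LOCF, and the plan also compares baseline characteristics of those with and without service-use data. Hospital records can continue after a missed interview, so 20% drop-out need not mean 20% missing cost. Early drop-out is reported as below 10%, and early loss is what drives the 3K term. Recall windows, scaling and the handling of CBT cost may be settled in a fuller document. All of this stands and limits the weight of the point. It does not remove it: the article names the method, and none of these facts makes it suitable for a summed cost.

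Four stronger readings are tempting, and the documents do not support them.

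- *LOCF creates a difference near £150.* The article gives neither a CBT cost nor a split of losses by visit, so no particular size is established.
- *The artefact always runs against CBT.* This needs savings spread over a long period. The Background fits savings in the first six months after treatment at least as well, and then losses after 12 months give a negative artefact.
- *LOCF makes an equivalence claim too easy.* Counting filled values as observed would narrow the interval from £118 to £105, but only if the SD stayed at £580. With a true difference of £0, an artefact of either sign makes equivalence harder to show. The two effects oppose each other, so no overall direction can be stated.
- *The same objection covers QALYs.* EQ-5D is a repeatedly measured level, and the argument about flows does not carry over to it.

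**Conclusion.** The point holds in limited form. LOCF is unsuitable for costs accrued over periods and summed to 24 months. If each form covers the time since the last, unscaled LOCF understates a flat-cost patient's total by 25%. It can also produce a between-arm difference when none exists, with equal drop-out: in the scenarios tabulated, from −0.2K to +K/3. Sign and size rest on three things the article does not give: the CBT cost, when savings fall, and when patients are lost. Some combinations give zero. With only £32–£45 of room between the CI half-width and the margin, even a modest artefact can change whether the interval lies inside ±£150.

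The consequence is that the robustness check cannot be interpreted. The complete-case primary result is not itself biased by LOCF.

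**What to change.** Replace LOCF for costs with multiple imputation, by arm, of period-specific costs (0–6, 6–12 and 12–24 months). Use hospital-record data wherever they exist, so that only the remainder is imputed. Enter CBT cost once, from sessions delivered, and never impute it or carry it forward. Add a sensitivity analysis that shifts the imputed costs by stated amounts in each arm, so that the reader can see how far the missing costs would have to differ before the equivalence conclusion changes. State the recall window of each service-use form.

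The cost is a change of wording in the analysis plan and a little more analysis work. No new data are needed, and the complete-case primary analysis can stay as it is.
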